## Abstract

**Background:**

Interstitial lung diseases (ILD), such as idiopathic pulmonary fibrosis (IPF) and non-specific interstitial pneumonia (NSIP), and chronic obstructive pulmonary disease (COPD) are severe, progressive pulmonary disorders with a poor prognosis. Prompt and accurate diagnosis is important to enable patients to receive appropriate care at the earliest possible stage to delay disease progression and prolong survival. Artificial intelligence-assisted lung auscultation and ultrasound (LUS) could constitute an alternative to conventional, subjective, operator-related methods for the accurate and earlier diagnosis of these diseases. This protocol describes the standardised collection of digitally-acquired lung sounds and LUS images of adult outpatients with IPF, NSIP or COPD and a deep learning diagnostic and severity-stratification approach.

**Methods:**

A total of 120 consecutive patients (≥ 18 years) meeting international criteria for IPF, NSIP or COPD and 40 age-matched controls will be recruited in a Swiss pulmonology outpatient clinic, starting from August 2022. At inclusion, demographic and clinical data will be collected. Lung auscultation will be recorded with a digital stethoscope at 10 thoracic sites in each patient and LUS images using a standard point-of-care device will be acquired at the same sites. A deep learning algorithm (*DeepBreath*) using convolutional neural networks, long short-term memory models, and transformer architectures will be trained on these audio recordings and LUS images to derive an automated diagnostic tool. The primary outcome is the diagnosis of ILD versus control subjects or COPD. Secondary outcomes are the clinical, functional and radiological characteristics of IPF, NSIP and COPD diagnosis. Quality of life will be measured with dedicated questionnaires. Based on previous work to distinguish normal and pathological lung sounds, we estimate to achieve convergence with an area under the receiver operating characteristic curve of > 80% using 40 patients in each category, yielding a sample size calculation of 80 ILD (40 IPF, 40 NSIP), 40 COPD, and 40 controls.

**Discussion:**

This approach has a broad potential to better guide care management by exploring the synergistic value of several point-of-care-tests for the automated detection and differential diagnosis of ILD and COPD and to estimate severity.

*Trial registration* Registration: August 8, 2022. ClinicalTrials.gov Identifier: NCT05318599.

**Supplementary Information:**

The online version contains supplementary material available at 10.1186/s12890-022-02255-w.

## Background

Interstitial lung disease (ILD) encompasses several pulmonary conditions defined by an alteration of the pulmonary interstitium, a restrictive pattern of lung function, and fibrotic scarring on chest computed tomography (CT). Approximately one-third of these disorders have known endogenous or exogenous causes, including environmental or occupational factors, infections, drugs and radiation. Two-thirds are of idiopathic aetiology [1] and comprise a range of subcategories, the most common of which is idiopathic interstitial pneumonia (IIP). In turn, IIP comprises a range of sub-pathologies, such as idiopathic pulmonary fibrosis (IPF) and non-specific interstitial pneumonia (NSIP) [2]. Identifying patients with IIP at the earliest possible stage is essential for care management as treatment is aimed at slowing the irreversibly debilitating and ultimately fatal progression. Delay in specialist referral is associated with a higher mortality, irrespective of disease severity [3]. With a mean delay of 2.2 years between the onset of symptoms and specialist referral, the investigation of competing diagnoses by non-specialist providers can be costly for both patients and healthcare providers [3]. However, given the initial non-specific symptomatic presentation, the need for advanced diagnostic tools, such as high-resolution chest CT (HRCT), and an expertise in the early-stage diagnosis of IPF and NSIP remain desirable and achievable objectives [4]. Distinguishing between IPF and NSIP raises considerable diagnostic challenges as their clinical presentations share many overlapping features. However, the distinction is useful as their response to treatment differs markedly [5]. Until now, with limited treatment options benefiting mostly patients in the early stages of the disease [6, 7], many patients will progress towards disability or death [8]. Despite research and advances in therapy, ILDs remain a worldwide health challenge affecting millions of people each year [9], emphasizing the need to make progress in diagnosis and prevention.

Different measures have been proposed to improve the early diagnosis of ILDs [10, 11]. In particular, the identification of the so-called “velcro”-like crackles on lung auscultation by primary care doctors has been suggested as an early and strongly predictive sign of IPF or fibrotic NSIP [4, 12]. For instance, while IPF and NSIP typically have fine velcro-like crackles audible on the mid-to-late inspiratory cycle, chronic obstructive pulmonary disease (COPD) tends to have coarse crackles occurring during the early inspiratory cycle [13]. As stethoscopes are readily available, inexpensive and non-invasive, they constitute an adequate tool to detect velcro-like crackles in the early stages of IPF or fibrotic NSIP to shorten the diagnostic delay and allow the prompt referral to specialised care. However, conventional auscultation is a highly subjective skill limited by inter-listener variability and human perceptual ability to distinguish between lung sounds and their temporal occurrence in the respiratory cycle. Inherent heterogeneity in stethoscope quality, background noise and patient-related factors, such as obesity or chest deformities, are other limiting factors. To overcome these drawbacks, research efforts have been devoted to improve computerised respiratory sound recording with electronic stethoscopes and an objective analysis based on advanced digital acoustic signal processing [14–17]. The advent of deep learning in recent years took the analysis of auscultation signals one step further by allowing an enhanced detection of abnormal lung sounds in patients with respiratory diseases [18–20].

Several studies have assessed the broad adoption and impact of deep learning to help diagnose COPD [21–23], the third leading cause of death worldwide [24]. The vast majority developed predictive models to cover a wide range of objectives, the main ones being the diagnosis and severity classification of the disease [25, 26]. A 2022 review of artificial intelligence (AI) techniques in COPD yielded 156 articles relevant to the application of AI in COPD research, including 56 concerning diagnosis, 65 on its prognosis, 54 on COPD severity classification, and 17 on the management of the disease [27]. Most studies have used a variety of features, including patient physiological characteristics, comorbidities, symptoms, vital signs, biomarkers, genomic information, pulmonary function tests, CT images, hospitalization information, and/or breath sounds [28, 29]. Regardless of the method(s) chosen, COPD remains an incurable and progressive disease and diagnosis at the early risk stage is important. In this sense, the work of Altan et al. is innovative. The deep learning algorithms they used on analysing multiple lung auscultation points for the early diagnosis of COPD achieved high classification performance rates [30, 31]. Achieving this with a method as conventional as lung auscultation can reduce the need for additional, more extensive, time-consuming, expensive or invasive diagnostic tests.

Conversely, research regarding IPF and NSIP are scarce and have focused mostly on datasets collected through radiological [32–34], genomic [35, 36] or functional tests [37]. Pancaldi et al. described the use of an AI algorithm to detect the presence of velcro-like crackles in patients with rheumatoid arthritis and a suspicion of ILD [17, 38]. However, to our knowledge, no study has investigated the benefit of deep learning-aided diagnostic tools for early IPF and NSIP diagnosis using respiratory sound analysis in adults. This might allow doctors to assess acoustic signatures more objectively and thus allow a more standardised and potentially earlier diagnosis in patients presenting at primary care clinics with non-specific, chronic respiratory symptoms. On the other hand, lung ultrasound (LUS) is already the standard of care for detecting consolidations, diagnosing pneumonia and guiding pleural taps. The distinction between A (normal aeration) and B (alveolar-interstitial syndrome) lines on LUS is clinically important and forms the backbone of multiple clinical decision trees for real-time respiratory diagnoses and treatment choices [39]. As such, not only is LUS a relevant gold standard for lung pathology, but it could also benefit from automation by deep learning.

We developed a series of deep learning algorithms on digital lung auscultation (*DeepBreath*) and LUS to detect a range of physiological and pathological lung diseases, including (COVID-19) [40]. This study will seek to explore the synergistic value of several point-of-care-tests for the AI-aided detection and differential diagnosis of ILD and COPD, as well as estimate of severity, with the aim to better guide and improve care management in adults.

## Methods

### Study design

This is a single-centre, prospective, population-based, case–control study that will be carried out in subjects with IPF, NSIP and COPD within a pulmonology outpatient clinic in Switzerland, with a total of approximately 7000 specialised consultations per year. Figure 1 shows the study flowchart and Table 1 details the study schedule. The present study protocol adheres to the Strengthening the Reporting of Observational studies in Epidemiology (STROBE) Statement [41].

**Fig. 1 Fig1:**
[figure not shown]
Study flowchart

**Table 1 Tab1:** Study schedule

	Study period		
	Pre-enrolment	Enrolment	Close-out
Timepoint	−*t*_1_	*t*_0_	
Study procedures			
Recruitment		✓	
Eligibility screening		✓	
Informed consent form		✓	
Assessments			
Case report form (demographic + clinical data)		✓	✓
EKO CORE digital auscultation collection		✓	✓
Pulmonary function tests		✓	
Chest CT-scan/X-ray	✓		
Lung ultrasound		✓	
K-BILD questionnaire		✓	
CAT questionnaire		✓	
SF-36 questionnaire		✓	

✓: Performed

### Population

Inclusion criteria are consecutive, consenting adult outpatients (> 18 years) with IPF (group 1), NSIP (group 2) and COPD (group 3) already diagnosed prior to the consultation (index) date. Probable and definitive IPF diagnosis will be made according to the Fleischner Society Consensus [42], NSIP diagnosis with the American Thoracic Society classification [2, 43], and COPD with the Global Initiative for Chronic Obstructive Lung Disease criteria [44]. Consenting, age-matched (± 2.5 years) individuals with normal lung function (spirometry, lung volume and transfer factor for carbon monoxide [TL_CO_]) followed in the outpatient clinic with a similar quality of electronic medical records, but for diseases other than the outcome of interest, will serve as the 1:1 control group (group 4). This latter group will comprise patients with obstructive sleep apnoea, follow-up of occupational lung diseases (miners, chemical workers, etc.), and follow-up of pulmonary nodules (considered benign after 2 years). Reasons for pulmonary follow-up among the controls will be reviewed and reported in a supplementary file. Identifying all cases with the outcome of interest and selecting controls for comparison is a more efficient and resource-sparing study design than a full cohort study. Exclusion criteria are: (1) patients who cannot be mobilised for posterior auscultation; (2) those known for severe cardiovascular disease with pulmonary repercussions; (3) patients known for a concurrent, acute, infectious pulmonary disease (e.g., pneumonia, bronchitis); (4) patients known for asthma exclusive from COPD; (5) patients with alpha-1-antitrypsin deficit; (6) a physical inability to follow procedures; and 7) inability to give informed consent.

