### Study procedure

The study will be performed over a period of 6 months. Recruitment can be stopped before the anticipated end if the inclusion of 160 patients is reached before. A trained research nurse/doctor ([name]) will recruit the subjects during a single routine consultation in the outpatient clinic. This will include checking the selection criteria for each patient prior to study participation, obtaining written informed consent, administering questionnaires on demographic characteristics (age, sex, occupation, long-term exposure to occupational or environmental agents, etc.), relevant medical history, and symptomatic presentation (Additional file 1), which will be captured by an electronic case report form to be completed by the study coordinator on a tablet. The nurse/doctor will also administer the standardised K-BILD [47], CAT [48], and SF-36 [49] severity assessment questionnaires, and record lung sounds during 5–7 min with an electronic stethoscope in the same zones as LUS acquisition, as previously proposed by our group [40]. For the LUS examination using a standard point-of-care ultrasound device, an adapted version of our previous 10-point acquisition protocol [50] will be used, which involves scanning the anterior superior, anterior inferior, posterior superior, posterior inferior and lateral thorax regions. In addition, pulmonary functional tests (conducted with patients in a stable condition) will be collected, as well as chest X-rays with two incidences (posterior-anterior and lateral) and HRCT scans for IIP patients (within 12 months). Controls will not be exposed to a chest X-ray and/or CT scan unless required as part of their routine follow-up; cases will have undergone such imaging given that it is part of their diagnostic evaluation.

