### Exploring the synergy of clinical data with breath sounds

Clinical data will be explored for its predictive capacity in the above tasks and added to the breath sound analysis either as a support vector machine (SVM) or in conditional feature extraction upstream of the neural network.

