## Questionnaires

Demographics including age, sex, ethnicity, environment (smoking status, long-term exposure to occupational or environmental agents, etc.), treatments, presence of chronic respiratory symptoms or repeated lower respiratory tract infectious diseases, as well as a diagnosis of other comorbidities (obesity, immunodeficiency, alpha-1 antitrypsin deficiency, etc.) will be reported in a questionnaire (Additional file 1). Severity of functional limitations according to the New York Heart Association (NYHA) functional classification [57] will be also reported if available.

The impact of IPF and NSIP on subjects’ health-related quality of life will be measured with the standardised K-BILD questionnaire [47] (use with license agreement), which covers 15 questions exploring 3 health dimension scores (psychological, breathlessness and activities, and chest symptoms) using a 7-point Likert response scale (scores range from 0 to 100, a higher score indicating better health status). The impact of COPD will be assessed with the CAT [48] (use with license agreement) that measures eight items: cough; phlegm; chest tightness; breathlessness; limited activities; confidence leaving home; sleeplessness; and energy. Scores range from 0 to 40, with a higher score indicating a more severe impact of COPD on a patient’s life. The SF-36 will also be used to assess the impact of IPF, NSIP or COPD on patients’ quality of life. The investigators will double-check on-site that the questionnaires are fully and accurately completed. Data collection will be carried out using the online REDCap database (REDCap, Vanderbilt University, Nashville, TN, USA; https://www.project-redcap.org/resources/citations/). Conditions or complaints occurring after enrolment will not be considered in the statistical analyses. Current symptoms at enrolment will be registered.

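### For ILD versus control, age-only matching and partly sleep-apnoea controls let sex, habitus and smoking feed the AUROC, and no stated analysis shows how much

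*Protocol article*

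**What the plan says.** **Control selection** (Protocol article, Population). Controls come from the same clinic, must have normal spirometry, lung volumes and gas transfer, and are matched on age within 2.5 years. No other patient characteristic is named for matching. On source: "This latter group will comprise patients with obstructive sleep apnoea", followed by occupational lung disease follow-up and pulmonary nodules judged benign. No share is set for any source. The section adds: "Reasons for pulmonary follow-up among the controls will be reviewed and reported in a supplementary file".

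**Habitus and sound** (Background). Among the limits of conventional auscultation, "patient-related factors, such as obesity or chest deformities, are other limiting factors".

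**Primary analysis** (Primary and secondary outcomes; Statistical analysis plan). ILD versus control is the first task of the primary outcome. Each task is reported as AUROC, sensitivity, specificity, predictive values and likelihood ratios with CIs over fivefold cross-validation. No adjustment, stratification or demographics-only comparator is named.

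**Related analyses that are planned:**
- Baseline demographic differences between cases and controls by conditional logistic regression (Statistical analysis plan).
- "Clinical data will be explored for its predictive capacity in the above tasks" (Exploring the synergy of clinical data with breath sounds). The secondary outcomes describe clinical data as signs, symptoms, demographics, history and basic tests.
- A model trained to detect crackles (secondary outcomes).

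**Variables collected.** Study procedure: "administering questionnaires on demographic characteristics (age, sex, occupation" and further items. Questionnaires: smoking status and "diagnosis of other comorbidities (obesity, immunodeficiency, alpha-1 antitrypsin deficiency, etc".

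**The concern.** The primary hypothesis is that ILD has its own acoustic and sonographic signature, which is more than saying the two groups can be told apart. The network is trained on time-frequency representations of the recordings and on ultrasound images. Nothing confines it to crackles, B-lines or the pleural line. If controls differ from ILD patients in chest-wall thickness, sex or smoking, those differences are available to it as a proxy for group.

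Cross-validation does not guard against this. Each held-out fold has the same selection of controls as the training folds, so a proxy that works in training also works in testing. The reported AUROC would then credit some non-pulmonary information to an ILD signature, and performance could fall in a population with a different mix of controls.

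**Working it through.** **The plan's own figures.** 40 IPF + 40 NSIP + 40 COPD + 40 controls = 160, which checks. The 40 per class and the AUROC above 0.80 are set by analogy to earlier work, without a formula, so neither can be recomputed.

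**Precision at the target.** Hanley-McNeil, A = 0.80, 80 ILD and 40 controls:
- Q₁ = A/(2−A) = 0.667; Q₂ = 2A²/(1+A) = 0.711.
- SE = √{[A(1−A) + 79(Q₁−A²) + 39(Q₂−A²)]/(80×40)} = 0.0397.
- 95% CI 0.72 to 0.88.

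**What non-disease traits could give alone.** The documents contain no sex, obesity or smoking figures by group, so all prevalences here are assumptions: controls versus ILD, obesity 60% v 25%, male 50% v 65%, ever-smoker 45% v 65%. Traits are taken as independent and read without error, and patients are ranked by likelihood ratio.

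- Obesity alone: 0.5 + |0.60 − 0.25|/2 = 0.675.
- Obesity and sex: AUROC is the sum over cells of (ILD share) × (half the control share in the cell + control share ranked below it).

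| Cell | Control | ILD | Contribution |
|---|---|---|---|
| Non-obese male | 0.20 | 0.4875 | 0.4875 × 0.90 = 0.4388 |
| Non-obese female | 0.20 | 0.2625 | 0.2625 × 0.70 = 0.1838 |
| Obese male | 0.30 | 0.1625 | 0.1625 × 0.45 = 0.0731 |
| Obese female | 0.30 | 0.0875 | 0.0875 × 0.15 = 0.0131 |
| Sum | | | 0.709 |

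- All three traits, same sum over eight cells: 0.736.
- Range for three traits: 0.66 with obesity 40% v 25%; 0.76 with 60% v 20%.

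**Imperfect reading.** A trait of prevalence p read with sensitivity and specificity s appears with prevalence ps + (1−p)(1−s). At s = 0.9, obesity becomes 58% v 30%, and the central three-trait AUROC falls from 0.74 to 0.69. At s = 0.8 it is 0.64. Without smoking, with obesity 40% v 25% and error-free reading, it is 0.62.

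**Cross-check with continuous BMI.** Let a share of controls have sleep apnoea and a BMI shifted upwards, add a sex difference, and fit a logistic model to simulated data:
- share 1/3, shift 0.5 SD, 10 points: 0.58;
- share 1/2, shift 1 SD, 20 points: 0.68;
- share 2/3, shift 1.5 SD, 30 points: 0.79.

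Only the last, extreme combination comes near 0.80, and it too assumes error-free reading.

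**Does the demographic comparison settle it?** Unmatched normal approximation, 80 v 40, two-sided 5%. For 60% v 80% male: null SE = √(0.2222 × 0.0375) = 0.0913; alternative SE = √(0.24/80 + 0.16/40) = 0.0837; power = Φ[(0.20 − 1.96 × 0.0913)/0.0837] ≈ 60%. For 60% v 75% it is about 36%. A non-significant difference would be weak reassurance, and the comparison does not involve the network's output.

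**The case against.** The strongest reply has four parts.

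1. **The imbalance is assumed.** The documents do not say that controls differ from ILD patients in BMI, sex or smoking, fix no share of sleep-apnoea controls, and mention obesity as a limit of human listening, not as a correlate of group. This stands: the size of the effect is conditional throughout.

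2. **The plan has safeguards.** Demographic differences are tested, reasons for control follow-up are reported, clinical data are examined for their own predictive capacity, and a crackle model is planned. The limitations acknowledge selection bias and call the study a pilot needing validation. This stands in part. It would be wrong to say that nothing planned bears on the question, and a demographics-only fit is compatible with the text. As described, though, demographics sit with symptoms and tests that reflect the disease, the crackle model does not show what the main network used, and the rest is descriptive.

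3. **The disease signal may dominate.** Sample size calculation expects velcro-like crackles in nearly all idiopathic interstitial pneumonia patients and no pathological sounds in controls. If so, the network should clearly beat any demographic benchmark. That is a reason to report the comparison.

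4. **A condensed article leaves such detail to the full plan.** True of analysis detail alone. Here the article fixes the control source and the matching variable, and states a primary analysis that cannot separate the two explanations.

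A reader might infer that an AUROC near 0.80 could be reached largely through confounding. The documents give no imbalance from which to conclude that, and the main assumed range stops at 0.76 even with error-free reading.

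**Conclusion.** The point holds for ILD versus control. Age is the only stated matching characteristic, sleep apnoea is a named control source, the protocol itself recognises obesity as affecting auscultation, and no stated analysis shows how much of the network's AUROC sex, habitus or smoking could account for.

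Under assumed imbalances these traits alone give about 0.66 to 0.76 if read without error, and about 0.69 in the central case at 90% accuracy. They could therefore explain a material part, but not all, of an AUROC near 0.80. The figures rest on prevalences that are not in the documents, on independence between traits, and on the traits being detectable in sound or image. Smoking is the least certain, because controls must have normal lung function.

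A reader might extend the point to ILD versus COPD or IPF versus NSIP. Control selection does not enter those tasks, so it does not apply there by this route. The change is worth making, but the point does not show that the design fails.

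**What to change.** For ILD versus control:

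- Fit, in the same cross-validation folds, a benchmark model using only age, sex, obesity (or BMI if recorded) and smoking. Report DeepBreath's paired AUROC difference from it with a 95% CI.
- Give AUROC by sex and by obesity as descriptive only. Under the assumed 60% v 25%, the obese stratum has 80 × 0.25 = 20 ILD and 40 × 0.60 = 24 controls, and the non-obese stratum 60 and 16. At AUROC 0.80 the Hanley-McNeil 95% CIs are about 0.66 to 0.94 and 0.69 to 0.91.
- Where several age-eligible controls are available, prefer those that balance sex.

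**Cost.** A small extra analysis on variables already to be collected, with no new visits or patients. The added value reported may be smaller than the raw AUROC. The difference will also be imprecise: with a benchmark AUROC of 0.74 (SE 0.045 by the same formula) and the network at 0.80 (SE 0.040), the half-width is 1.96 × √(0.045² + 0.040²) ≈ 0.12 if the two are uncorrelated, and less if they are positively correlated. It should be read as an estimate, not as a pass or fail test.

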## Pulmonary function tests and chest CT scan

For all subjects, spirometry, body-plethysmographic parameters (see details above) and lung diffusion capacity for carbon monoxide (TLco/Kco) will be measured. Participants’ lung images recorded from previous HRCT (or X-rays) during past routine visits will be used. No chest CT scans will be performed as part of this study; only lung images of participants previously recorded as part of their regular follow-up or to be performed in this context will be used. The presence on the chest CT scan of honeycombing, traction bronchiectasis, reticulations, ground-glass opacities, and emphysema will be measured for patients with IPF, NSIP or emphysema. The main chest CT scan features of IPF are reported to be basal and peripheral reticulations, traction bronchiectasis, minimal ground glass opacities, and moderate or extensive honeycombing. For NSIP, the CT scan typically demonstrates bilateral lung involvement and invariably some extent of ground-glass opacities, mainly in the lower zones with fibrotic changes, while honeycombing is not a common feature [55]. The presence on the chest CT scan of structural abnormality, such as ≥ 5% emphysema and/or ≥ 15% gas-trapping and/or airway wall thickness ≥ 2.5 mm [56], will be measured for patients with COPD. The protocol assumes normal lung parenchyma in the control group, which will not be exposed to radiation unless controls have already undergone a recent (i.e., < 5 years) chest CT scan for other reasons. This will be taken into consideration as we will investigate the association of lung sounds with radiological characteristics.

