### Sample size calculation

Each patient will provide 10 audio recordings of 30 s. Samples will be considered at the patient level with all 10 recordings. In deep learning, sample size calculation is an intractable problem that is usually discovered through empirical investigation. The number of samples required to reach a certain performance criterion is dependent on the characteristics of the dataset, the diversity and number of the classes, the degree of data augmentation possible, as well as the complexity of the learning algorithm. Thus, sample size calculations cannot rely on the traditional statistical heuristics that are often used in biostatistics. Rather, sample size estimations in deep learning are mostly made by analogy. Evaluating existing knowledge on similar datasets, we find that the expected proportion of velcro-like crackles in IIP patients is nearly 100% [4], whereas the prevalence of coarse crackles is 71% in COPD patients [58]. The exclusivity of these sounds among groups is not known, but overlap is assumed to be minimal and pathological sounds are by definition absent in non-ILD and non-COPD control subjects. Assuming a similar discriminative power compared to a previous work done by our group (personal communication) to distinguish between normal and pathological lung sounds in pneumonia from 80 patients in balanced classes (40 pathological; 40 controls) with 8 auscultation sites of 30 secs each, we estimate using the same number of patients in each class to achieve convergence at above 80% of the area under the receiver operating characteristic curve (AUROC). Thus, we will aim to enrol at least as many patients in each group: 80 ILD (40 IPF, 40 NSIP); 40 COPD; and 40 controls (i.e., known not to have ILD or COPD, and with normal lung function). As the recruitment site would expect 120 ILD patients (40% with IPF; 60% with NSIP) and 100 with COPD over the space of one year, this number is achievable in the time frame of the study (6 months), even with a 70% consent rate.

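### Controls followed for occupational lung disease are labelled ILD-negative on normal lung function and assumed normal parenchyma, with no imaging check

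*Protocol article*

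**What the plan says.** All references are to the protocol article.

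- **Population** builds the control group from three sources: sleep apnoea, pulmonary nodules, and "follow-up of occupational lung diseases (miners, chemical workers, etc". Controls must be "individuals with normal lung function (spirometry, lung volume and transfer factor for carbon monoxide" included, and must attend the clinic "but for diseases other than the outcome of interest, will serve as the 1:1 control group (group 4". The nodule source carries a condition of its own (judged benign after two years); the occupational source carries none. Seven exclusion criteria follow, and none names occupational or other interstitial disease. The reasons for follow-up will be reviewed and reported, but no exclusion or analysis depends on that review.
- **Background** says of ILD that roughly a third of cases "have known endogenous or exogenous causes, including environmental or occupational factors".
- **Pulmonary function tests and chest CT scan** states: "The protocol assumes normal lung parenchyma in the control group". No CT is done for the study. **Study procedure** confirms that controls have chest imaging only where routine care calls for it.
- **Sample size calculation** describes "40 controls (i.e., known not to have ILD or COPD, and with normal lung function", and adds that "pathological sounds are by definition absent in non-ILD and non-COPD control subjects".
- **Primary and secondary outcomes** makes discrimination of ILD from controls the first task. **Primary objective** words it more widely, as ILD against non-ILD sounds and images.

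**The concern.** A control source defined by lung disease of occupational origin is placed in the ILD-negative class, although the protocol links that kind of cause to ILD. Cases have imaging as part of their diagnostic work-up; controls need none. For these controls, the documents do not say how freedom from ILD is known.

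If some of them have interstitial or other parenchymal change that nobody has recognised, an algorithm that correctly picks it up is scored as making a false-positive error. Apparent specificity and AUROC fall, and the network is trained to treat that signal as normal. The section on lung ultrasound credits the method with high sensitivity to subtle subpleural change, so this is the sort of finding that the second modality could bring out. The statement that controls have no pathological sounds, which supports the sample-size argument, would also lack a basis in this subgroup.

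**Working it through.** **The plan's own figures.** The group sizes add up: 40 IPF + 40 NSIP + 40 COPD + 40 controls = 160. The performance target, AUROC above 0.80, is set by analogy with earlier work, so there is no formula to reproduce.

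**What secures the control label.** Three statements protect it: normal lung function, follow-up for something other than the outcome of interest, and the description of controls as known to be free of ILD and COPD. The first is a measurement. The second and third exclude ILD that has been recognised. None is a check for change that has not been recognised, and the CT section describes parenchymal normality as an assumption.

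**Illustration of size.** The documents give neither the share of occupational controls nor the rate of interstitial change among them, so both the share and the true AUROC below are assumptions. Let a share c of controls have the same score distribution as ILD cases. A case then outranks such a control with probability 0.5, and

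apparent AUROC = (1 − c) × A + c × 0.5, where A is the true value.

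For A = 0.85 and c = 1/40 = 0.025: 0.975 × 0.85 + 0.025 × 0.5 = 0.841. For c = 4/40 = 0.10: 0.90 × 0.85 + 0.10 × 0.5 = 0.815.

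| True AUROC | 1 of 40 | 2 of 40 | 4 of 40 | 8 of 40 |
|---|---|---|---|---|
| 0.80 | 0.793 | 0.785 | 0.770 | 0.740 |
| 0.85 | 0.841 | 0.833 | 0.815 | 0.780 |
| 0.90 | 0.890 | 0.880 | 0.860 | 0.820 |

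The share that brings the apparent value down to 0.80 is (A − 0.80)/(A − 0.50). That is 0% at A = 0.80, 0.05/0.35 = 14% at A = 0.85, and 0.10/0.40 = 25% at A = 0.90.

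Specificity behaves in the same way. With true sensitivity and specificity both assumed to be 0.85, four mislabelled controls give 0.90 × 0.85 + 0.10 × 0.15 = 0.78.

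**Set against sampling error.** The Hanley-McNeil standard error at AUROC 0.80 with 80 ILD cases and 40 controls is 0.040, so the 95% interval is 0.80 ± 1.96 × 0.040, about 0.72 to 0.88. A shift of 0.01 to 0.04 lies well inside it.

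**The case against.** The strongest reply is that the protocol already keeps ILD out of the control group. Controls must be followed for something other than the outcome and be known not to have ILD. The Background's own definition of ILD includes a restrictive pattern, which normal spirometry and lung volumes would rule out. This largely stands. A reader might infer that the plan admits ILD patients as controls by rule, and the text does not support that. Nor does it say that interstitial change can coexist with normal lung function; that remains a possibility that the plan leaves unchecked. The same definition also includes scarring on CT, and CT is what controls are not required to have.

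Second, the Background says that occupational factors can cause ILD, not that occupational lung disease is ILD. The enrolled cases are IPF and NSIP, so ILD of occupational origin is not clearly the target of the primary outcome. This also stands, although the Primary objective's wider wording, ILD against non-ILD, leaves such a patient wrongly labelled.

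Third, the phrase is explained by occupations (miners, chemical workers), not diagnoses, and may mean surveillance of exposed workers. If so, the text should say so.

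Fourth, the protocol is open about its assumption. It says that prior CT in controls will be taken into account, reports reasons for follow-up, and lists control selection as a limitation. But that limitation concerns representativeness, not label error, and no rule says what happens when an existing image is abnormal.

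Finally, the illustration is a worst case per control, since each mislabelled control scores exactly like an enrolled case, and under it the bias cannot manufacture a favourable result. Both points are accepted.

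**Conclusion.** The concern holds in a limited form. The defect is unverified ILD-free status in one control subgroup. Unrecognised interstitial or other parenchymal change could be labelled ILD-negative in the first primary task, and the claim that pathological sounds are absent from controls by definition is not secured.

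The size is unknown. Under the mixture model, each mislabelled control of 40 costs about 0.0075 (true AUROC 0.80) to 0.010 (true AUROC 0.90), always downward. The model takes the classifier's scores as given, so any effect of wrong labels on training is not counted. A few mislabelled controls could not be told from sampling error afterwards, so eligibility is the place to deal with them.

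A reader might go further and conclude that all controls with occupational lung disease should be dropped. The documents do not support that as a clear gain: the Primary hypothesis also proposes that ILD signatures differ from those of other respiratory diseases, and such controls make the negative class more demanding.

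**What to change.** 1. **Population:** exclude from the controls anyone with a diagnosed occupational interstitial or parenchymal lung disease, and anyone whose chest X-ray or CT already on record shows interstitial change. Keep exposed workers under surveillance who have no such diagnosis. If surveillance was all that was meant, reword the source accordingly.
2. **Statistical analysis plan section:** report ILD versus control AUROC and specificity for all controls, then without the occupational controls, and without the controls who have no prior imaging. With at most 40 controls these comparisons are descriptive.
3. **Pulmonary function tests and chest CT scan, and Sample size calculation:** state normal parenchyma and absent pathological sounds as assumptions, checked where imaging exists.

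The cost is eligibility wording, a look at images already on file, and one sensitivity analysis. No new imaging or radiation is involved. The pool for age-matched controls narrows slightly, but two other sources remain, only 40 controls are needed, and the clinic has about 7000 consultations a year. The negative class also becomes somewhat easier to separate from ILD, which may raise apparent performance; the report should state this.
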